#### **f. Obtaining Informed Consent**

The investigator will obtain signed informed consent from students and parents to collect measures before enrollment to the study. The blood draw is a voluntary measure for this study and a separate informed consent from students and parents will be collected (Appendix C). Students and parents will be recruited through a TX Sprouts Study Information Packet sent home to the parents in students' weekly homework folders. The TX Sprouts Study Information Packet will contain: an information letter, the Parental Permission, and Parental Informed Consent (Appendix D). Parents who are interested will be asked to sign the Parental Permission- Assent Form, collect the signature from their child, and complete the Parent Survey at baseline and post-intervention. They will return these documents to the child's teacher through the homework folder. Consent forms may be returned without the signature of the student. If this should occur, a research staff member will read the information to the student and collect his / her signature. Their choice not to participate in the study will be honored, when applicable. We will also set up TX Sprouts information booths at school events such as "Back to School" night, PTA meetings, and other school events where parents will be present to collect parent and student consent form signatures. We will also include information about our project in newsletters and email announcements to the parents (see recruitment flyer in Appendix E). Teachers, staff, and GLC will also be asked to sign a consent form prior to the interview or being audio recorded (see Appendix F).

[figure not shown]

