**Aim 1:** To test the effect of the Sprouts intervention on the following changes in health outcomes for the child: a) FV intake; b) dietary psychosocial variables; c) anthropometric parameters (e.g., BMI, WC, percent body fat); d) metabolic risk factors (e.g., blood pressure, metabolic syndrome, fasting glucose, insulin, and lipids); and e) home environment (e.g., availability and accessibility of FV).

***Hypothesis 1:*** Sprouts intervention students compared to control students will have, as primary outcomes: increased vegetable intake and reduced BMI z-scores, WC, fasting glucose, and insulin; and, as secondary outcomes: increased fruit and fiber intake and reduced added sugar intake, improved dietary psychosocial variables (i.e., preference and motivation, self-efficacy for FV), and reduced body fat and other metabolic risk factors.

**Aim 2:** To test the effects of the TX Sprouts intervention on changes in dietary intake and related dietary psychosocial variables of the parents.

**Hypothesis 2:** TX Sprouts intervention parents compared to control parents will have increased FV intake, improved psychosocial variables linked to FV intake, and improved access and availability of FV in the home.

**Exploratory Aim:** To identify specific strategies/components of the TX Sprouts intervention that were implemented and sustained at the completion of the intervention, which will provide valuable information on how to disseminate and sustain long-term garden programs in schools.

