**Garden Leadership Coalition (GLC):** We will establish GLCs at each of the schools during the intervention phase, which will facilitate some of the school-level components of the intervention. These GLCs will be comprised of interested teachers, school staff, senior citizens, parents, and children, but these groups will be different and unique at each school site. . Given that the CATCH program is currently being implemented in all participating school districts as the state-mandated coordinated school health programs, we will enlist the CATCH Champions and Wellness Committees at each school to be a part of the GLC. Key personnel (Drs. [name], [name], [name], and [name]) have considerable experience with coalition building in schools. We will employ a GLC Coordinator to help form and organize GLCs at each school site and serve as the liaison between the GLCs and the Sustainable Food Center (SFC), a nationally recognized Austin-based non-profit organization that promotes gardening and health eating in a culturally relevant manner. SFC has developed and currently teaches School Garden Leadership Trainings across the Austin area. SFC will host a Garden Leadership Training workshop during the intervention phase and will then teach a series of three workshops to the GLCs in the subsequent year. Currently, SFC offers several workshops, including: Basic Organic Gardening classes (which includes information on planting fruit trees, rain water collection, fence building, and gardening in pots/containers), Farm Direct classes (which connect local growers with schools), and La Cocina Alegre (a series of family cooking classes using fresh produce). The GLC Coordinator will work with the GLCs to select and provide these workshops to the schools; the cost of the workshops will be covered by this grant. The grant will also pay for an AgriLife Extension Coordinator to help provide local Master Gardener volunteers to work with the GLCs to help maintain the gardens and sustain the gardening program. As part of the Extension Master Gardener program, all volunteers undergo a 3-month training program and then must complete 50 hours of volunteer work the first year and 30 hours of volunteer work every year after, so this partnership is ideal for their program as well as the school sites. The GLC coordinator, the Extension Coordinator, and the Master Gardener volunteers will continually help connect the GLCs to local stakeholders, including local agricultural producers, community gardens, food pantries, food banks, and senior citizen centers. GLCs will be encouraged to meet before or after school twice a month in the beginning and at least monthly for the remaining years. The GLCs will be responsible for holding design-build meetings and for planning and implementing the Garden Kick-Off and Harvest Celebration events. GLCs will develop an action plan to engage school maintenance staff, teachers, and other community members to get involved in the program as well as reach out to garden sponsors and local foundations to fundraise in subsequent years. Other potential strategies that the GLC might employ include: hosting family plant and harvest days throughout

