**School Lessons:** All 3rd-5th-grade students in the participating schools will receive the curriculum as part of their normal school day. We will hire bilingual nutrition and garden educators who have experience teaching nutrition/ gardening programs to teach the TX Sprouts curriculum in the Intervention year. All educators will undergo a weeklong training course led by the research and Extension staff that will cover all material/activities taught during each lesson, structure and flow of each class, cooking and preparation

skills needed to make recipes in curriculum, classroom preparation/clean up procedures, logistical issues with teaching in garden, how to complete process logs, and any issues with supervising student volunteers. The schoolteachers will “shadow” our educators during these lessons the first year. Twenty TX Sprouts lessons (each 30-45 minutes in length) will be taught by our educators separately to each 3rd-5th grade classroom throughout the school year as part of their normal school day. Before the program is implemented, we will work with stakeholders in each school district to decide exactly where and when these lessons can be taught and incorporated into normal school days.

***Family Lessons at Schools:*** The bilingual garden/nutrition educators will also teach monthly TX Sprouts lessons throughout the school year for the families of participants at each of the schools, for a total of nine lessons. Each lesson will be taught by a bilingual gardening/nutrition educator and will consist of a 60-minute lesson that parallels the topics taught during the student lessons. We will incentivize the parents to attend the lessons by offering free meals, produce, groceries, and free babysitting for younger siblings.

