### **TX Sprouts Research Evaluation:**

Evaluation measures will be collected at baseline and end of the school year in both treatments (intervention and control schools). Measurements will occur during the first four weeks of school in the fall and the last four weeks of school in the spring. Most measures on children will be collected at the schools during normal school hours. The fasting blood draws will occur first thing in the morning before school starts. The following evaluation measures will be obtained from students at baseline and post-intervention:

- Measured height, weight, BMI parameters, waist circumference (WC), body composition (via bioimpedance); carotenoid scan of skin
- Blood pressure via child-specific automated cuff;
- Subsample of students will complete three 24-hour diet recalls by telephone;
- Child survey assessing dietary intake via food screener and related determinants of dietary behaviors (e.g., preference/motivation/self-efficacy to eat FV);
- Program lessons may also be audio/visual recorded;
- Voluntary fasting blood sample to assess glucose, insulin, and lipid parameters;
- Accelerometers to measure physical activity;
- Time on Task observations

Parent questionnaires will be handed out or mailed to the homes after consent is obtained at baseline and post-intervention. Questionnaires are translated into Spanish, culturally appropriate, and take ~60 minutes to complete. We will encourage parents to complete the questionnaire before the first family lesson and return it via mail (pre-paid postage will be provided). However, parents will also be able to complete the questionnaire at the first and last lessons. Parent surveys will evaluate the following: food security via USDA validated questions, confidence cooking, dietary intake via validated screener, reported height and weight, medical history, basic demographics, child feeding practices and food home environment from CEBQ and TGEQ, and preferences adapted from Domel et al. We will also attempt to measure height and weight on a subsample of parents, which will occur at the first and last parent lesson. Parent workshops may also be audio/visually recorded.

After the intervention year, we will conduct a series of structured interviews (30 minutes or less per interview) as well as surveys, with participating school stakeholders (i.e., principals, teachers,

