**Figure 1: Flow of participants through study**

## **7. Privacy and Confidentiality**

Privacy will be maintained through out the experiment. The questionnaires will be filled out in the presence of only a researcher in a classroom. The Time on Task field notes will be handwritten and transferred to a computer. The contact information will be entered into a computer spreadsheet.

- Any audio and video recordings will be stored securely and only the research team will have access to the recordings. Recordings will be kept for 3 years and then erased. Only study staff will have access to this data. This original data will not be shared with other researchers.
- All blood samples will be kept in a locked freezer in [name] laboratory. All blood samples will be associated with a code rather than their identifiable data.
- The subject data collected with the questionnaires, anthropometric measures, interview, Time on Task observation, and any contact information given on the form will be associated with a code rather than their identifiable information. The master key that can link the subject to their data will be stored in a separate, locked location and only designated research staff will have access to this file. The computer files will be password protected and only accessible by designated research staff. All identifiable data collected from this study will be stored for 3 years and then destroyed.

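### The protocol gives conflicting return routes for the Parent Survey, the source of all Aim 2 outcomes, and two of them are linked to trial arm

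*Protocol*

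**What the plan says.** **Consent section (6.f, Obtaining Informed Consent).** Interested parents sign the permission and assent form, obtain the child's signature, and "complete the Parent Survey at baseline and post-intervention". The next sentence reads: "They will return these documents to the child's teacher through the homework folder". No sealed envelope or other protection is mentioned.

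**Evaluation section (4, TX Sprouts Research Evaluation).** Questionnaires are handed out or mailed home after consent. Parents are encouraged to complete them before the first family lesson and "return it via mail (pre-paid postage will be provided"). A third option follows: "However, parents will also be able to complete the questionnaire at the first and last lessons".

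**What the survey feeds.** Aim 2 (section 3) concerns "changes in dietary intake and related dietary psychosocial variables of the parents", and Hypothesis 2 adds access to and availability of fruit and vegetables in the home. Parent intake is measured by a 10-item screener (section 5, Dietary Intake).

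**Who takes part, and when.** Schoolteachers shadow "our educators during these lessons the first year" (section 4, School Lessons). On the Garden Leadership Coalitions: "These GLCs will be comprised of interested teachers, school staff, senior citizens, parents, and children". Control schools receive the programme, including family lessons, only in the year after their wave's post-testing (section 4, Delayed Intervention to Control Schools). Section 8 (Compensation) provides a $15 incentive for each completed questionnaire packet, distributed at the parental lessons.

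**The concern.** A self-report outcome should be collected in the same way in both arms. Here the protocol has two incompatible instructions for the instrument behind every Aim 2 outcome, so schools or waves could follow different ones without breaking the text.

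The routes are also not neutral between arms. At post-test an intervention parent's answers about fruit and vegetables may pass through a teacher who has spent the year in the programme being evaluated, or may be written at a lesson led by the study's educators. A control parent meets neither situation. If either setting shifts answers, or if access to lessons and incentives shifts who returns a survey, the shift falls on one arm. It then adds to or subtracts from the estimated effect. It cannot be separated from that effect in analysis, because the protocol describes no objective check on parent intake.

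The survey also asks about food security and medical history (section 4), and parents are asked to report income (section 5). Passing these answers through school staff unsealed is an avoidable confidentiality risk.

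**Working it through.** The contradiction itself involves no arithmetic, so the check sets the sections side by side.

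**1. Does the teacher route cover the survey?** The sentence before the return instruction lists the signed form, the child's signature and the survey at both time points. The literal antecedent therefore includes the survey.

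**2. Is it the only route?** No. Section 4 gives two others and encourages mail. Nothing ranks section 6.f against section 4.

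**3. Is each route available equally in both arms during the measurement year?**

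| Route | Intervention schools | Control schools |
|---|---|---|
| Pre-paid mail (section 4) | Available | Available |
| Child's teacher (section 6.f) | Teacher has shadowed lessons by post-test and may sit on the coalition | Teacher has no programme role until after post-testing |
| First and last family lessons (section 4) | Available, taught by study educators | No lessons that year |
| Incentive at parental lessons (section 8) | Available | No lessons that year; no other means stated |

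Only mail is the same in both arms. I read the coalitions as forming in the year a school receives the programme, which is how the delayed intervention is described.

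**4. When would a difference act?** Baseline falls in the first weeks of school, when teachers have had little or no exposure to the lessons. The teacher-linked difference would therefore arise mainly at post-test. The lesson option and the incentive differ by arm at both time points.

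**5. Does any safeguard close the gap?** Section 7 states: "The computer files will be password protected and only accessible by designated research staff". It also restricts the master key and has the data held under a code. These rules cover data once the study holds them. They do not cover a paper survey on its way through a teacher.

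**6. Can the size be derived?** No. The protocol gives neither the split of surveys by route nor any estimate of reporting bias. Even the precision against which a bias would be judged is unclear. For parents, Table 2 gives a variance of 0.08, an ICC of 0.071 and 64 parents per school. With 8 schools per arm,

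SE = √[2 × V × (1 + 63 × 0.071) / (8 × 64)].

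- If 0.08 is the within-school variance, as labelled: V = 0.08 / (1 − 0.071) = 0.086 and SE = 0.043 servings/day.
- If 0.08 is the between-school variance: V = 0.08 / 0.071 = 1.127 and SE = 0.155. This reading reproduces the table's parent school counts of 12, 16, 18 and 24.

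The two readings differ by a factor of about 3.6.

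**The case against.** The strongest reply is that section 6.f is about consent. The information packet it describes holds a letter, the permission form and the consent form, with no survey listed. The sentence after the return instruction concerns consent forms that come back unsigned by the student. A post-intervention survey cannot travel back with a recruitment packet. The instruction may therefore mean only the signed forms, with the survey clause stating what parents agree to do later. This is a fair alternative reading and it stands as a possibility. It does not remove the need to reconcile the sections, because the literal reading is equally open to staff in the field. It also leaves the lesson option and the incentive arrangement untouched.

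Secondly, a reader might infer that teachers see the answers and so bias them. No section says that teachers open or read surveys. The text makes them at most a conduit, and a desirability effect is a plausible inference only.

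Thirdly, intervention parents know they received the programme, whatever the route, and the study team that would receive mailed surveys also delivers it. Part of any desirability bias would remain after the fix. This is correct, and the fix should not be presented as a cure.

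Finally, a reader might infer an inflated type I error rate, or a breach of section 7. Neither is supported. An error rate would need an assumed bias, for which the protocol gives no basis, and a choice between two standard errors that differ almost fourfold. Section 7 restricts computer files and the master key, so its silence on paper in transit is a gap and not a contradiction.

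**Conclusion.** Sections 4 and 6.f contradict each other on how the Parent Survey is returned, and section 6.f, read literally, routes it through the child's teacher unprotected at both time points. Two of the three routes, and the incentive, are linked to arm in the measurement year. Parents' self-report and return rates are therefore open to arm-specific differences, mainly at post-test. Direction and size are unknown.

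This rests on the literal reading of section 6.f for the teacher route. For the lesson route and the incentive it rests only on the stated timing of the delayed intervention. It concerns Aim 2. The children's five primary outcomes (vegetable intake, BMI z-score, waist circumference, glucose and insulin) do not come from this survey. The point is an inexpensive improvement worth making, not evidence that the Aim 2 results would be biased.

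**What to change.** - In section 6.f, limit return to the teacher through the homework folder to the permission and assent forms.
- In sections 4 and 6.f, state one return route for the Parent Survey, identical in both arms and at both time points: either the pre-paid mail already planned, or a sealed, code-labelled envelope that school staff do not open.
- Drop completion at family lessons, or restrict it to the same sealed procedure. Aligning section 6.f with section 4 as it stands would not be enough, because the lesson option exists only in intervention schools that year.
- In section 8, give the survey incentive in the same way in both arms, not through lessons that control parents do not have.
- Record the return route for every survey, so that its balance between arms can be reported.

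The cost is protocol wording, envelopes and one extra data field; pre-paid postage is already planned. The downside is a possibly slightly lower return rate if mail alone is used, which the sealed envelope would largely avoid.

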**Figure 1: Flow of participants through study**

## **7. Privacy and Confidentiality**

Privacy will be maintained through out the experiment. The questionnaires will be filled out in the presence of only a researcher in a classroom. The Time on Task field notes will be handwritten and transferred to a computer. The contact information will be entered into a computer spreadsheet.

- Any audio and video recordings will be stored securely and only the research team will have access to the recordings. Recordings will be kept for 3 years and then erased. Only study staff will have access to this data. This original data will not be shared with other researchers.
- All blood samples will be kept in a locked freezer in [name] laboratory. All blood samples will be associated with a code rather than their identifiable data.
- The subject data collected with the questionnaires, anthropometric measures, interview, Time on Task observation, and any contact information given on the form will be associated with a code rather than their identifiable information. The master key that can link the subject to their data will be stored in a separate, locked location and only designated research staff will have access to this file. The computer files will be password protected and only accessible by designated research staff. All identifiable data collected from this study will be stored for 3 years and then destroyed.

## **8. Compensation**

A subsample of children will complete three 24-hour diet recalls and we will provide any child that completes at least two diet recalls with a \$10 gift card. These gift cards will be handed out in person at their schools. If participants cannot obtain their gift cards at school, a check will be mailed home to them. Students will also receive \$15 in incentives throughout the study to participate, including a study t-shirt, water bottle and cooking utensils. These incentives will be handed out during TX Sprouts lessons throughout the school year. In addition, students will receive a small toy (\$1) immediately after completing the evaluation measures at baseline and post intervention. In order to get participation in the blood draws, we will offer the child a \$20 cash incentive for each blood draw, which will be given immediately after the draw. We will provide the -screening results to the parents, which will be mailed to the parent, within one month of the test (See Appendix G). We have used these approaches with success in LA Sprouts. Parents will receive \$15 in incentives (groceries, cooking supplies, etc.) at baseline and post-intervention for each completed questionnaire packets (pre- and post-intervention they will be compensated for completing the questionnaire). We will email, text or call parents to remind them to complete and return surveys. The incentives will be distributed to parents during the parental lessons.

